#### Hypothesis 2a (Prescription Opioids—Combined Effect)

To test the hypothesis that prescription opioid use will be associated with worse outcomes on driving performance (SMS), we will conduct a 2-sample *t* test to see if SMS differs in prescription opioid users versus nonprescription opioid users, regardless of medical marijuana use status. Then, similar to aim 1, we will use ANCOVA to test the relationship between SMS and prescription opioid use; the variable selection process will be based on the significance of variables and the adjusted *R*^2^, while the medical marijuana use status will not be included in the list of variables for the selection. This will tell us if prescription opioid use affects driving performance regardless of medical marijuana use status. Additionally, if the best-fitted model contains different covariates from the best model for medical marijuana use seen in aim 1, we will also perform a model to adjust the same covariates as in aim 1 to compare the results for prescription opioid use and for medical marijuana use. This will allow us to see which one alone has a bigger effect on driving performance when adjusting for the corresponding and the same covariates.

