### Sample Size and Power

Power estimates for this study are based on the number needed for the subanalysis to ensure we have sufficient power to answer aim 2. Using G*Power for the *F* test, we calculated the sample size for a small effect size (*f*=0.20) based on the expectation of a smaller effect size for subgroup analyses than for the main analyses [36]. Therefore, with an α of 0.5 and power set at 80%, a total sample size of 198 is needed to detect a small effect between subgroups of medical marijuana only, medical marijuana and prescription opioids, prescription opioids only, and no use at all. However, to ensure we have the full sample needed, we are planning for a potential early termination rate (eg, drive not completed due to intoxication or other reasons) of 5%, which indicates we need a sample size of 250—as 198 + 10 (5%) = 250 (125 per group). We anticipate a medium effect size for aim 1 based on the first ROAD ACE (Reactions of Older Adults Driving After Cannabis Exposure) project (1R21DA048067) that examined driving errors and medical marijuana 7-day pattern of use in a driving simulator. We found a Pearson *r*=0.459, which is equal to a medium effect size (see preliminary data above). Therefore, we will have sufficient power to test the effects in aims 1 and 2.

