### Study Conditions

#### Exposure: Medical Marijuana Group

Any patient who has been certified for medical marijuana use and has held an active medical marijuana card in the state of Florida for at least 12 months, is aged 50 years or older, endorses chronic or severe pain, and reports using medical marijuana purchased through the state of Florida dispensation system daily or most days of the week for the past year, as documented by purchases over the course of the year in the OMMU database, has an active Florida driver’s license and the visual acuity to perform the task with or without vision corrective apparatus (glasses or contacts). Medical marijuana was legalized in Florida in January 2017. Per Florida state statute 381.986, residents of Florida have access to marijuana for medical use if authorized by a qualified medical marijuana physician. All medical marijuana patients must register with the state for access to medical marijuana, which includes the certification process identifying a qualifying condition, the reason the patient is authorized to use medical marijuana, and tracking all purchases through the OMMU. Qualified medical marijuana patients are allowed to purchase up to 2.5 ounces of smokable flower every 35 days, and limits on the milligrams of all other routes of administration are set by the physician. Patients must be recertified to use medical marijuana every 210 days (7 months). We will track dosage, frequency, type of product used (high vs low cannabidiol/THC), and route of administration. All medical marijuana participants will be recruited from the MMTC, our medical marijuana recruitment partner. Participants will be allowed to complete the drive regardless of a negative or positive urine screen for opioid use. Our current data suggests that approximately 40% of medical marijuana patients will also test positive for opioid use.

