#### No Marijuana Use Group (Past 10 Years)

NMG participants will be race-sex–matched adults aged 50 years and older who endorse chronic or severe pain, recruited from the community using flyers and handouts, newspaper advertisements, internet advertisements, social media, in-person lectures and events, and contact by mail, email, and the infrastructure and support of Oak Hammock at the UF—a residential retirement community. We will also phone individuals enrolled in the UF Clinical and Translational Science Institute’s Integrated Data Repository, a database organizing clinical information across UF Health’s clinical and research programs [42]. Individuals enrolled in UF Health services or taking part in UF research studies can provide consent to be contacted within this system, and data can be queried using National Institutes of Health’s Informatics for Integrating Biology and the Bedside tool, which provides researchers with a HIPAA-compliant and UF Institutional Review Board–approved limited dataset [43]. In querying this dataset for adults aged 55-84 years (adults aged 45-54 years were grouped together and thus excluded from the query) with who endorse chronic or severe nonmalignant pain, the tool reported 7463 potential participants who have consented to be contacted for research participation. Participants will be allowed to complete the drive regardless of a negative or positive urine screen for opioid use. Our current data suggests that approximately 25% of control participants will also test positive for opioid use, with literature estimating of up to 50% of patients with chronic or severe nonmalignant pain using opioids.

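### Hypothesis 2a bars marijuana status from the opioid model, so its result cannot show an opioid effect independent of marijuana

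*Protocol article*

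**What the plan says.** Under Hypothesis 2a (Prescription Opioids—Combined Effect), the protocol article plans three steps.

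- First, a "2-sample *t* test to see if SMS differs in prescription opioid users versus nonprescription opioid users, regardless of medical marijuana use status".
- Second, an ANCOVA of the sum of maneuvers score (SMS) on opioid use. Covariates are chosen by significance and adjusted R², "while the medical marijuana use status will not be included in the list of variables for the selection". The stated reading is: "This will tell us if prescription opioid use affects driving performance regardless of medical marijuana use status".
- Third, if the selected covariates differ from those of aim 1, a further opioid model with the aim 1 covariates, so that the two exposures can be compared: "This will allow us to see which one alone has a bigger effect on driving performance".

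The expected opioid rates are given under Study Conditions. For the medical marijuana group (MMG), "approximately 40% of medical marijuana patients will also test positive for opioid use". For the no marijuana group (NMG), "approximately 25% of control participants will also test positive for opioid use". The same sentence also cites a higher published figure: "literature estimating of up to 50% of patients with chronic or severe nonmalignant pain using opioids".

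**The concern.** Two things must hold for marijuana status to confound the opioid comparison: it must be associated with opioid use, and it must affect driving. The protocol expects the first (40% against 25%). The second is its primary hypothesis, and Sample Size and Power anticipates a medium effect for aim 1. Under those expectations, a pooled opioid contrast partly compares marijuana users with non-users.

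The exclusion is a stated rule, not a detail left to a later document, and it works against the conclusion that the protocol draws from it. An opioid effect that holds whatever the marijuana status needs adjustment for that status or stratification by it.

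At the expected rates, and if marijuana worsens driving, the bias makes opioids look worse, which is the direction Hypothesis 2a predicts. The comparison of the two exposures is also affected, because its opioid side is never adjusted for marijuana. The protocol intends its results to inform risk screening and intervention targets.

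**Working it through.** **Plan's own figure.** The protocol gives no figure for this contrast. Its nearest is the aim 2 sample size of 198. An F test with 1 numerator df, f = 0.20 and α taken as 0.05 needs 199 (power at 198 is 79.96%), so 198 is reproduced to within one. The bias below does not depend on the total sample size. Only the false-positive rates do, and they use the planned 250.

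**Inputs**
- 125 per group (Sample Size and Power).
- Opioid-positive: MMG 40%, NMG 25%; literature upper figure 50% (Study Conditions).
- Marijuana effect d, in within-cell SDs of SMS, as a worsening. The protocol gives no SD for SMS, so d is an assumption: 0.5 as a medium effect, range 0.2 to 0.8.
- True opioid effect set to zero.

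**Step 1: marijuana mix by opioid status**
- Opioid users: 125 × 0.40 + 125 × 0.25 = 50 + 31.25 = 81.25. MMG share: 50/81.25 = 61.5%.
- Non-users: 75 + 93.75 = 168.75. MMG share: 75/168.75 = 44.4%.
- Gap: 0.6154 − 0.4444 = 0.171.

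**Step 2: bias of the unadjusted contrast**
- Bias = gap × d. At d = 0.5: 0.171 × 0.5 = 0.085 SD.

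**Step 3: false-positive rate of the t test (two-sided 0.05, normal approximation)**
- The variance within each opioid group is 1 + d² × share × (1 − share): 1.059 for users and 1.062 for non-users. The pooled SD is 1.030.
- SE = 1.030 × √(1/81.25 + 1/168.75) = 1.030 × 0.1350 = 0.139.
- Shift = 0.0855/0.139 = 0.61 SE.
- Rejection probability = [1 − Φ(1.96 − 0.61)] + Φ(−1.96 − 0.61) = 9.4%.
- In 10,000 simulated trials at d = 0.5, the pooled analysis gave a mean bias of 0.085 SD and 9.2% rejections. With marijuana status in the model, the bias was 0.00 and the rejection rate 5.1%.

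**Step 4: range.** Each cell shows the bias in SD and, in brackets, the false-positive rate. A positive bias makes opioids look worse.

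| NMG opioid rate | Gap | d = 0.2 | d = 0.5 | d = 0.8 |
|---|---|---|---|---|
| 25% | 0.171 | 0.034 (5.7%) | 0.085 (9.4%) | 0.137 (15.6%) |
| 40% | 0 | 0 (5.0%) | 0 (5.0%) | 0 (5.0%) |
| 50% | −0.101 | −0.020 (5.3%) | −0.051 (6.7%) | −0.081 (9.1%) |

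The last row uses 50 + 62.5 = 112.5 opioid users (MMG share 44.4%) and 75 + 62.5 = 137.5 non-users (54.5%).

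**Step 5: does another part of the plan repair it?**
- The extra model with aim 1 covariates does not bring marijuana status back. In aim 1 marijuana is the exposure, not a covariate.
- Hypothesis 2b refits the aim 1 model separately in marijuana users and non-users and aims to describe the four exposure cells. Opioid contrasts within those groups would be free of this problem if opioid use is entered, which the text does not state. They still leave the 2a test and the comparison of the two exposures as they are.
- The Alternative Design Plan deals with the distribution of the outcome, not with confounding.

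**The case against.** The best defence is that Hypothesis 2a only asks about the overall association of opioid use with driving, and that Hypothesis 2b then looks within marijuana groups. A pooled association is a legitimate description, and 2b does mean that 2a is not the only opioid evidence. But the protocol reads 2a as an effect that does not depend on marijuana status and builds a comparison of the separate exposures on it. A pooled association supports neither.

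A second objection is that the size is uncertain. This stands. The 0.17 rests on 40% against 25%, and every participant has chronic or severe pain, so the cited 50% could apply to the control group. Since the sign is then unknown in advance, this is an argument for adjusting.

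A third is that the two exposures would be compared with matching covariates. This also stands, and it answers a complaint about differing covariate sets. It does not answer the absence of marijuana status from the opioid model.

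A reader might go further than the document allows in four ways.

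- **That the ANCOVA also carries 17% of the marijuana effect.** The figure is derived for the unadjusted contrast. Selected covariates related to either exposure could raise or lower it.
- **That aim 1 is confounded by opioids in the same way.** Aim 1 adjusts for significant clinical variables, among others, and does not bar opioid use. The exclusion is in 2a only.
- **That the false-positive rate reaches about 21%.** This needs the cited r = 0.459 converted to d = 1.03 as if it compared two equal groups. The protocol describes it as relating simulator driving errors to a 7-day pattern of use, and calls it medium.
- **That the pooled estimate describes no real population.** The protocol says under Strengths and Limitations that representativeness is not its aim, so this is a preference and not an error.

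**Conclusion.** The point holds for Hypothesis 2a. The rule that excludes marijuana status contradicts the interpretation that the protocol attaches to the result, and nothing else in the document corrects the 2a test or the comparison of the two exposures.

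At the protocol's own expected rates, the unadjusted opioid contrast takes up about 0.17 of any marijuana effect. For an assumed effect of 0.5 SD that is 0.085 SD, with about 9% false positives instead of 5%. This is modest, and it depends on the opioid rate in the no marijuana group: no bias at 40%, and −0.051 SD with about 6.7% false positives at 50%. If marijuana has no effect on SMS, there is no bias from this source. The size in the ANCOVA cannot be given from the document. The exclusion in 2a does not touch the aim 1 comparison of marijuana groups.

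**What to change.** - Delete the sentence that keeps marijuana status out of the variable selection, and force marijuana status into every Hypothesis 2a model whatever its significance.
- Estimate the opioid and marijuana effects from one model with common covariates. Base the statement on which is larger on the difference between those two coefficients, with a confidence interval.
- Keep the pooled t test as descriptive only.

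The cost is a short change of text and one degree of freedom out of 250 planned participants. Both exposures are already recorded, so data collection does not change. Recruitment is expected to run to 2029, which leaves time to make the change before analysis.

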#### Hypothesis 2b

Then we will check the combined effect of medical marijuana and prescription opioid on driving performance (SMS) using ANCOVA. The best fitted model we find in aim 1 will be performed in the subgroup of medical marijuana users and non–marijuana users, respectively. Thus, we will have a clear picture of the driving performance in the 4 groups: medical marijuana and prescription opioid, medical marijuana without prescription opioid, prescription opioid without medical marijuana, and no medical marijuana no prescription opioid. Thus, the combined effect can be determined.

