**Objective:**

This study aims to document the observational trial protocol. The primary goal of this study is to identify the effects of daily long-term (ie, use for >12 months daily or most days of the week) medical marijuana use on driving performance outcomes using an open-road driving performance task under real-world conditions in adults aged 50 years and older who endorse chronic or severe nonmalignant pain and to examine the combined effect of daily long-term medical marijuana use and prescription opioid use on driving outcomes. A secondary goal is to qualitatively explore self-regulation of medical marijuana and prescription opioid use in this population.

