### Hypotheses Testing

#### Hypothesis 1a and 1b (Driving Performance—Between-Group Analyses)

To answer the question of whether long-term medical marijuana use affects behavioral driving outcomes, we will compare the SMS between MMG and NMG using an independent 2-sample *t* test. ANCOVA will then be used to determine whether the two groups differ on SMS by adjusting for significant sociodemographic, driving, behavioral, and clinical variables. A model-building approach, which will include age, will be used, and analyses will be performed with and without covariate adjustment, since sample-dependent variables may explain some outcome variance. Tukey’s honestly significant difference test or Tukey-Kramer test will be used to estimate the clinical significance of the findings.

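### Hypothesis 2b fits separate models in marijuana users and non-users and commits to no test of the combined effect of marijuana and opioids

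*Protocol article*

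**What the plan says.** The Objective in the abstract includes, within the primary goal, the aim "to examine the combined effect of daily long-term medical marijuana use and prescription opioid use on driving outcomes". Sample Size and Power bases the whole sample size on aim 2. It uses a G*Power F test with f = 0.20 and 80% power, and arrives at a total of 198 for a comparison between four exposure subgroups.

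Hypothesis 2b opens with "Then we will check the combined effect of medical marijuana and prescription opioid on driving performance (SMS) using ANCOVA". The next sentence defines the method: "The best fitted model we find in aim 1 will be performed in the subgroup of medical marijuana users" and, separately, in the subgroup of non-users. It then lists the four marijuana-by-opioid cells and concludes "Thus, the combined effect can be determined".

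The aim 1 model is described under Hypothesis 1a and 1b: "ANCOVA will then be used to determine whether the two groups differ on SMS by adjusting for significant sociodemographic, driving, behavioral, and clinical variables". Its exposure is marijuana group, and no opioid term is named. Hypothesis 2a compares opioid users with non-users, "while the medical marijuana use status will not be included in the list of variables for the selection".

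**The concern.** A combined effect is a statement across the four cells. It is either the difference between people exposed to both drugs and people exposed to neither, or the extent to which the opioid effect differs by marijuana use. Two separate within-group models state neither quantity. The aim 1 exposure cannot be estimated inside a group where everyone has the same value. If opioid use takes its place, the output is two opioid effects, adjusted with different covariate slopes and residual variances, and nothing in the plan says how they are to be compared.

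At stake is a question that belongs to the primary goal and drives the sample size. With no contrast fixed in advance, the easy course is to set the two p-values side by side, which is not a test of a difference.

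**Working it through.** **1. Does any other section supply the missing test?**

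- Hypothesis 1a and 1b: marijuana group plus covariates. Tukey comparisons are named here, for two groups only.
- Hypothesis 2a: marijuana status is kept out of variable selection, so no interaction is possible.
- Data Analysis Plan: finite mixture and generalized linear models are mentioned in general terms, with no marijuana-by-opioid term.
- Alternative Design Plan: a contingency for distributional problems.

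None names an interaction, a joint four-cell model or a contrast between strata.

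**2. The plan's own figure of 198.** Take a noncentral F with λ = f²N, f = 0.20 and power 0.80. Read alpha as 0.05; it is printed as 0.5, which is a separate error.

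- Numerator df 1: N = 199, and power at 198 is 0.7996. This reproduces the figure.
- Numerator df 3 (omnibus test of four groups): N = 277, and power at 198 is 0.64. This does not reproduce it.

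The numerator df is not stated. On either reading the sizing test uses the whole sample, and the two subgroup fits are not that test.

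**3. Cells.** There are 125 per group. The expected opioid-positive share is about 40% in the marijuana group and 25% in the comparison group (Study Conditions).

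- Marijuana group: 0.40 × 125 = 50 with opioids, 75 without.
- Comparison group: 0.25 × 125 ≈ 31 with opioids, 94 without.

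**4. What a side-by-side reading would do.** Assume opioids lower the score by the same d SD in both groups, so there is no interaction. Let p1 and p2 be the two-sided 5% t-test powers in the two groups. Then P(significant in one only) = p1(1 − p2) + p2(1 − p1). At d = 0.4 this is 0.585 × 0.517 + 0.415 × 0.483 = 0.50.

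| d (SD, assumed) | p1 (50 v 75) | p2 (31 v 94) | Significant in one only |
|---|---|---|---|
| 0.2 | 0.19 | 0.16 | 29% |
| 0.3 | 0.37 | 0.30 | 45% |
| 0.4 | 0.585 | 0.483 | 50% |
| 0.5 | 0.78 | 0.67 | 41% |
| 0.6 | 0.90 | 0.82 | 24% |
| 0.8 | 0.99 | 0.97 | 4% |

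With 5% loss (N = 237.5) the values at 0.3, 0.4 and 0.5 SD are 44%, 50% and 42%.

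**5. What one pooled model could detect.** The interaction contrast is the difference in differences Δ. In SD units its variance is 1/50 + 1/75 + 1/31.25 + 1/93.75 = 0.076, so SE = 0.276. In balanced cells Δ = 0.8 SD corresponds to f = 0.8/4 = 0.20, the planning value.

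| N | Δ = 0.8 SD | Δ = 0.4 SD |
|---|---|---|
| 250 | 0.82 | 0.30 |
| 237.5 (5% loss) | 0.80 | 0.29 |
| 250, comparison-group opioid share 50% | 0.88 | 0.34 |

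The 50% share is the upper literature figure that the protocol gives.

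**The case against.** The strongest reply is that a joint analysis was intended and remains possible. Hypothesis 2b opens by promising an ANCOVA of the combined effect, and the sizing section describes an F test between the same four cells. Listing four cells makes sense only if opioid use enters each subgroup model, so the missing term is loose wording. Once it is there, the strata are independent samples. The difference between the two opioid effects has standard error √(SE1² + SE2²), and hence an interval and a p-value. Both-versus-neither can be had by taking adjusted means at common covariate values. Letting slopes and variances differ by stratum is a modelling choice, not an error.

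All of that stands. A reader might infer that the combined effect cannot be estimated from the planned fits; the documents do not support this. What they support is narrower: the only model described is stratified, and the plan never commits to the contrast.

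Two further inferences should be resisted. No section says that significance in one group will be set against non-significance in the other, so the 50% figure is not the error rate of a stated rule. It is also close to the peak of a curve that falls away on both sides. Nor should the sizing be described as an omnibus four-group test, because 198 matches a 1 df test.

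Finally, Study Design defines the estimand only as marijuana group versus comparison group. That aim 1 comparison is untouched.

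**Conclusion.** The point holds in its narrow form. Hypothesis 2b fixes a method, declares that it determines the combined effect, and specifies no interaction, joint contrast or comparison across strata. This is not a detail left to an analysis plan: the protocol names a procedure, and that procedure stops short of the question. The consequence falls on the second half of the primary goal and on the analysis that justifies the sample size.

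The size of the problem depends on how the results would be read. Under a side-by-side reading by significance, a spurious contrast between groups would appear in about 4% to 50% of studies across equal effects of 0.2 to 0.8 SD. The assumptions are a common SD, no gain from covariates, two-sided alpha of 0.05, the protocol's expected opioid shares of 40% and 25%, and no dropout. The effect sizes are assumed; the protocol gives none for opioids.

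**What to change.** Replace the separate fits in Hypothesis 2b with one ANCOVA in all participants, containing marijuana group, opioid use, marijuana × opioid and one common covariate set. Report the four adjusted means, the both-versus-neither contrast and the interaction contrast, each contrast with a 95% confidence interval. Label any within-subgroup fits as descriptive. State in Sample Size and Power which of these contrasts the 198 refers to.

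The change is one of wording and uses the same data. About 30 of the planned 250 participants had been enrolled by November 2025, so it can be made early in recruitment.

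The limitation should be written beside it. The planned size carries an interaction of 0.8 SD (power about 0.82 at 250) but not one of 0.4 SD (0.30 to 0.34). The interval should therefore carry the interpretation, and a non-significant interaction must not be reported as absence of interaction.
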